## 4. Materials and Equipment

### 4.1. SDR-tES Intervention

Our tES paradigm uses a protocol developed by Teledyne with identical frequency and waveform characteristics for the slow-oscillatory tES paradigm described originally by Marshall and colleagues [16]; only, it is to be applied during wakefulness. The device interfaces wirelessly with a cell phone over low-energy Bluetooth and is controlled from an easy-to-use application.

#### 4.1.1. Stimulation Frequency

We will apply the stimulation over 2 sets of anode/cathode pairs. Anodes are located approximately at the frontopolar 1 (Fp1) and frontopolar 2 (Fp2) locations, as measured in the standard 10–20 EEG electrode system. Cathodes are placed on the ipsilateral mastoids. We will use a pulsed direct current waveform at a frequency of current oscillation at 0.75 Hz.

#### 4.1.2. Stimulation Protocol

PeakSleep™ is a constant current device that delivers a stable stimulation as a function of the impedance measured across the two sets of medical grade hydrogel electrodes (Axelgaard Little PALS; Axelgaard Manufacturing, Fallbrook, CA, USA), which achieve skin impedances in the 20–50 kOhm range (a DC impedance measurement) and carry low sensation, typical of other tES devices. The device gradually increases its peak stimulation current, limited to a range between 100 and 500 A per electrode. Devices are configured to deliver 100 stimulation trains over 30 min, where each train has 6 pulses of a 0.75 Hz trapezoidal stimulation. The inter-train interval is 10 s, leading to a total stimulation time of <14 min with a maximum dose of 1 mA (500 μA per electrode pair). We will limit the total stimulation time to 30 min per day at the prescribed intensities in accordance with the recommended best practices. Our selected stimulation protocol falls within the appropriate range of current published guidelines on best practices for the safe application of tES in most cases [14].

### 4.2. Sham Condition

Devices will be configured to deliver a low amplitude (e.g., 100 μA) waveform of a different frequency (e.g., 25 Hz) for the same treatment duration. The purpose of the sham stimulus is to control for any placebo effect arising from the sensation of the stimulation. Beyond these differences in the frequency and amplitude of stimulation, devices will be operated in exactly the same way during the sham treatment. Participants and investigators will both be blinded as to their assignment, and only the study monitor will know the assignment of treatment conditions.

### 4.3. Device Safety

The devices are contained in individual pelican cases that are easy to store in a secure manner. Participants will be advised not to share the device and to secure it when not actively in use. Additionally, the device has a safety check that prohibits more than 40 min of use in a given 24 h period. Therefore, if others are using the device in addition to the patient, the patient will know about it and will be instructed to contact the research staff.

## 5. Detailed Procedure

### 5.1. Visit 1 (Enrollment)

If the participant meets all inclusion criteria, informed consent will take place prior to any experimental procedures. Once consent is given and participants understand the full scope of the study procedures, they will be asked to complete a demographics questionnaire, the patient health questionnaire (PHQ-9), the Posttraumatic Stress Disorder (PTSD) Checklist for DSM-5 (PCL-5), the State Trait Anxiety Inventory (STAI) and the Headache Impact Test (HIT). Suicidal ideation is one of the exclusion criteria for further participation indicated by item 9 on the PHQ-9. Any participant responding to this item with a score > 0 will be interviewed by the PI, and if further medical attention is deemed necessary, the participant will be dismissed from any further participation and referred to the appropriate medical help. If a participant fails to meet the inclusion/exclusion criteria for the study, then all data from screening materials (PHQ-9, PCL-5, STAI, HIT, ISI) will be deleted. Participants will be offered compensation of up to USD 1000 for the completion of the study, with an opportunity to receive compensation at the completion of each in-person visit. A detailed schedule of assessments to be collected during the 8-week study can be found in Table 2.

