### 2.5. Eligibility Criteria

Participants are eligible if they are at least 18 to 70 years old, have been diagnosed with sleep-onset insomnia or a self-reported insomnia diagnosis (Insomnia Severity Index score ≥ 15), have sleep onset latency > 30 min 6 months prior to enrollment, and no pharmacologic or non-pharmacologic treatment for insomnia in the last 14 days, including sedating medications at bedtime. Patients who meet any of the exclusion criteria (see Table 1) on the day of consent will be excluded.

After potential participants are selected, the study team will obtain informed consent approved by the USU Institutional Review Board (IRB). Participants will be free to withdraw consent and discontinue participation at any time without prejudice. In addition, the PI may end a participant’s participation in this study for any of the following reasons: (1) if the participant develops any condition that in the judgment of the PI may place them at risks not described above or at greater severity for those described above by continuing his/her participation; (2) if the participant becomes pregnant; (3) if the participant is unable to keep his/her scheduled sessions; (4) if the study is halted by the sponsor, the IRB, or the FDA; and (5) for administrative reasons.

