## Figures and Tables

**Figure 1 clockssleep-07-00003-f001:**
[figure not shown]
PeakSleep™ senses brain activity using three EEG sensors on the forehead and delivers a current through two pairs of hydrogel electrodes located on the forehead and matched to ipsilateral mastoid locations.

**Table 1 clockssleep-07-00003-t001:** Exclusion criteria.

Exclusion Criteria:
1. Neurologic conditions that include seizures or increase their risk, including recent, multiple, or severe concussion or traumatic brain injury, stroke, multiple sclerosis, or cognitive impairment. 2. Any psychiatric disorder requiring weekly or more frequent clinical monitoring or medication changes in the last 4 weeks. 3. A history of neurodevelopmental disorders such as attention deficit hyperactivity disorder, a learning disability, or developmental delay. 4. Any inpatient hospitalization or major surgery or medical procedure within the past 6 months. 5. Hearing impairments requiring implanted or external devices for amplification. 6. Current substance use disorder within the past year, not including nicotine. 7. The current use of narcotics or opioid-based medications for the treatment of pain with or without a prescription within the last year. 8. Change in psychotropic (non-sleep-related) medications within the last 4 weeks. 9. Consuming more than 10 alcoholic beverages per week. 10. Treatment of drug or alcohol use/abuse within the past 1 year. 11. Sleep disorders that require treatment other than insomnia. 12. Any motor coordination deficits that interfere with the use of the tES device. 13. Participants should not have trauma/cuts/rashes on their forehead or behind the ears that would interfere with wearing the device or cause discomfort for the research subject. 14. Tattoos on the head. 15. Non-removable metal anywhere in the body except bridges or fillings, including pacemakers, defibrillators, cochlear implants, brain implants including deep brain stimulators, or other implanted devices. 16. Any suicidal attempts within the last 12 months. 17. Any other condition that the investigator believes would prevent the completion of the study or put the participant at risk. 18. Any suicidal ideations or thoughts of self-harm within the last 2 weeks. 19. Pregnant or believes there is a chance of pregnancy. ^1^

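### Table 1 excludes any suicidal ideation in the last 2 weeks, but section 5.1 makes dismissal after a positive PHQ-9 item 9 depend on medical need, so one outcome is left inconsistent

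*Protocol article*

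**What the plan says.** Three places in the protocol article bear on this.

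- **Table 1, item 18** lists as an exclusion: "Any suicidal ideations or thoughts of self-harm within the last 2 weeks". It carries no severity threshold and no discretion clause.
- **Section 2.5 (Eligibility Criteria)** gives the table its force: "Patients who meet any of the exclusion criteria (see Table 1) on the day of consent will be excluded".
- **Section 5.1 (Visit 1)** names the instrument: "Suicidal ideation is one of the exclusion criteria for further participation indicated by item 9 on the PHQ-9". The next sentence sets the procedure: "Any participant responding to this item with a score > 0 will be interviewed by the PI". Its second half ties both removal from the trial and referral to the investigator finding, at that interview, a need for more medical care.

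Section 5.1 also has the screening data, including the PHQ-9, deleted for anyone who does not meet the eligibility criteria. Section 2.4 uses the PHQ-9 to assess suicidal ideation as a possible psychiatric adverse effect. Sections 5.3 and 5.5 and Table 2 repeat the PHQ-9 at Visits 3 and 5.

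**The concern.** The eligibility rule turns on whether ideation is present. The Visit 1 procedure turns on whether the investigator thinks medical attention is needed. These are different tests, and a person can meet the first without meeting the second. The document does not state one consistent outcome for that person.

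Three things depend on the answer.

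1. **Exposure.** It decides whether someone with recent ideation receives an investigational stimulation device for which the protocol itself lists psychiatric effects as possible. Enrolling a person whom Table 1 excludes would be an eligibility deviation in a safety-sensitive group.
2. **Data retention.** If the person counts as failing the criteria, the screening PHQ-9 is deleted. If not, it is kept as the baseline record.
3. **Reading of the safety outcome.** If positive responders can be enrolled, a positive item 9 at Visit 3 or 5 may have been present before treatment. If they cannot, it has arisen since screening.

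**Working it through.** There is no arithmetic here: the point involves no sample size, power, event count or error rate. The check is a comparison of the rules, case by case.

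**Are the rules about the same thing?** Item 18 is the only ideation criterion in Table 1; item 16 concerns attempts. Section 5.1 describes PHQ-9 item 9 as the indicator of the ideation exclusion, so the document itself links the two, and nothing needs to be assumed about the recall period of item 9. The timing also matches: section 2.5 applies the criteria on the day of consent, and Table 2 places both consent and the PHQ-9 at Visit 1.

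**What does each rule do?**

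| Item 9 at Visit 1 | Interview finding | Section 2.5 with Table 1 item 18 | Section 5.1 procedure |
|---|---|---|---|
| 0 | no interview triggered | not excluded by item 18 on this indicator | no action |
| above 0 | medical attention necessary | excluded | dismissed and referred |
| above 0 | medical attention not necessary | excluded | no dismissal stated |

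The first two rows agree. In the third row, Table 1 excludes, while the section 5.1 procedure gives no instruction to dismiss.

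**Is section 5.1 consistent within itself?** Not fully. Its first sentence on ideation treats it as an exclusion. The next makes removal depend on a further condition. If every positive answer already excluded, the condition attached to dismissal would have no work to do. That is why the wording implies that some positive responders remain. It is an implication, because no sentence says that they may.

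**Do the downstream effects follow?** Yes, from the third row. Being excluded there brings the deletion sentence of section 5.1 into play; not being excluded does not. The same split decides whether the participants assessed with the PHQ-9 at Visits 3 and 5 can include people who were positive at Visit 1.

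**The case against.** The strongest reply is that no true conflict exists. Section 5.1 nowhere permits a positive responder to continue; it is silent on the case where medical attention is not needed. Staff could interview every positive responder, refer those who need help, and still exclude everyone with ideation under Table 1, without breaking a sentence of the protocol. This part stands. A reader might infer that section 5.1 expressly gives the investigator discretion to enrol, or that the two rules cannot both be followed. The documents support neither inference.

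A second reply is that the interview only verifies what a questionnaire answer means. That would be a sensible reading if the test were whether ideation had occurred. The stated test is need for medical attention. An investigator could confirm recent ideation, judge that no medical attention is needed, and find no instruction to dismiss in this procedure.

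A third reply is that the conditional clause is only an escalation pathway, with Table 1 still governing eligibility. The clause, however, covers dismissal from participation as well as referral, and the document gives no order of precedence.

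A fourth reply points to safeguards. Every positive responder is interviewed, exclusion 17 bars anyone the investigator believes would be put at risk, section 2.5 lets the investigator end participation on grounds of risk, and the PHQ-9 is repeated. These stand as partial safeguards. They limit the consequence but rest on the investigator's judgement or come later, so they do not settle the outcome at Visit 1.

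Finally, a journal article condenses a fuller protocol. That would answer a complaint about missing detail. Here both rules are printed, and they point in different directions.

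**Conclusion.** The point holds as an inconsistency confined to one case: item 9 above 0 with further medical attention not deemed necessary. Section 2.5 and Table 1 exclude that person, while section 5.1 implies that the person may stay. It does not hold as a claim that section 5.1 grants permission to enrol or that staff are unable to comply with both passages.

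The documents do not give the share of candidates with a positive item 9, or how many of those would be judged not to need medical attention, so the number affected is unknown and may be small. No statistical figure in the article changes: the primary outcome, sample size and planned analysis are untouched. The point matters because it concerns participant safety, eligibility and the reading of the PHQ-9 as a safety measure.

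The conclusion rests on the document's own statement that item 9 indicates the ideation exclusion, and on reading the dismissal condition as it is written.

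**What to change.** The sponsor and investigator must reconcile section 2.5, section 5.1 and Table 1 item 18 so that the same single outcome for an item 9 score above 0 appears in all three. The text should state that outcome explicitly for the case where the interview does not find further medical attention necessary. This review does not say which rule is right.

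Once the rule is settled, the deletion sentence in section 5.1 and the use of the PHQ-9 in section 2.4 should be checked against it, so that it is clear whether a Visit 1 positive answer is retained and whether a later positive answer can be read as new since screening.

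The cost is a change of protocol wording and an ethics notification. No recalculation is needed.

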#### 5.1.1. Actigraphy Device Training

The participant will be trained on the device and asked to wear the actigraphy device (FitBit) continuously for the next 2 weeks. The first two weeks of the study involve collecting baseline sleep assessment data with a particular focus on identifying a pre-intervention SOL, which is the primary outcome.

#### 5.1.2. Subjective Questionnaire Training

Participants will then be informed of when and how to complete the required daily sleep diary for the next two weeks. Cumulatively, Visit 1 may take up to 1 h.

### 5.2. Visit 2 (Treatment 1)

Participants are block-randomized to treatment conditions based on the order (sham or stimulation first) and will be balanced with respect to gender. Participants who successfully complete 2 weeks of baseline collection will be enrolled in the first treatment group of their assigned order. To assess their insomnia baseline, they will complete the Insomnia Severity Index (ISI) during this visit. They will be trained on the use of the PeakSleep™ device and sent home for 2 weeks. The PeakSleep™ device will deliver therapy and collect EEG data for the investigation of neural activity for both stimulation and sham conditions. The participant’s response to the first treatment condition will also be measured with actigraphy and a daily sleep diary completed on a phone app, which also controls the PeakSleep™ device.

#### Initial Headset Training Session

The individual will participate in a training session on how to use the headset device. Participants will complete a short (5 min) trial session to demonstrate that they know how to use the device and to monitor any short-term adverse reactions to the stimulation prior to home use. Visit 2 is expected to take about 30 min.

### 5.3. Visit 3 (Washout)

During Visit 3, we will collect PeakSleep™ devices and administer a second ISI to assess participants’ response to treatment condition 1. Participants will also be requested to fill out a short questionnaire asking about the occurrence and details of any adverse events during the past two weeks with the device, which the investigator will review during the visit. Participants will complete another PHQ-9 to reassess any impact on depression or suicidal ideations. Participants will return home without the PeakSleep™ device but will continue to wear the actigraphy devices and complete the daily sleep diary in order to monitor sleep habits during a 2-week washout period. The purpose of the washout interval is to investigate any lingering effects from the first intervention and to ensure that those receiving the stimulation first return to a proper baseline prior to the sham treatment. Visit 3 will take approximately 1 h.

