### 2.2. Primary Outcome

We intend to measure the reduction in SOL between sham and stimulation groups using FitBit actigraphy data collected during baseline, treatment, and washout periods.

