### 3.2. Statistical Analyses

Our primary outcome, the change in SOL from baseline as measured via FitBit actigraphy, will be assessed over 14 days of treatment data by constructing a linear mixed effects model accounting for age, baseline SOL, ISI severity, and prior sleep medication use. The changes related to the arm receiving the treatment first will be compared to those achieved by the group receiving the sham first, avoiding any persistent effects of the PeakSleep device. As a secondary outcome, within-subject comparisons between the treatment and sham will also be made using a linear mixed effects model, which will include the order as an additional covariate. Other secondary outcomes will be compared by similarly modeling the objective measures (TST, WASO) and subjective measures obtained at various timepoints across the trial (ISI, PHQ-9). To investigate the differences in sleep measures between treatment groups, we will analyze actigraphy data by evaluating measures of central tendency (the median within a patient and across nights) in each condition (the mean across patients comparing stimulation and sham treatments) imported into MATLAB (R2020). All measures will be investigated as differences from each patient’s individual baselines.

The immediate effects of the stimulation will also be investigated among physiological data, including heart rate and electroencephalography. Changes in heart rate variability and EEG spectral power will be assessed pre- versus post-stimulation, comparing intraindividual changes from baseline between the treatment and sham. For EEG spectral analysis, we will use MATLAB (R2020) to compute spectral power in each frequency band in response to each stimulation event.

The statistical significance of differences between treatment groups for each measure will be tested using either a Wilcoxon Rank Sum test or a paired Student’s *t*-test, depending on whether the data occupy a normal distribution. We will also perform a two-way ANOVA to investigate differences due to sex and the treatment order. A participant’s data will be assessed for inclusion in the study at each visit contingent on obtaining viable data in at least 8 out of the 14 daily sessions during each 2-week period, including viable actigraphy data and the accompanying sleep diary data, successful application of the PeakSleep™ intervention, and adverse events.

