### 5.4. Visit 4 (Treatment 2)

Participants who were assigned to the stimulation treatment group during Visit 2 will be assigned to the sham group and vice versa. Participants will take the ISI once again for a second baseline measurement and will be sent home for the final 2 weeks to collect data on their responses to the second treatment condition. Their response to the second treatment condition will be measured with actigraphy and a daily sleep diary. EEG data will also be collected again from PeakSleep™ for the investigation of neural activity. Visit 4 will take approximately 30 min.

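### The secondary within-subject comparisons are open to carryover, and the washout nights and Visit 4 ISI that could show it have no stated role in the analysis

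*Protocol article*

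**What the plan says.** All references are to the protocol article.

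- **Washout (5.3).** It has two purposes: to look for lingering effects of the first intervention, and "to ensure that those receiving the stimulation first return to a proper baseline prior to the sham treatment". Participants "will continue to wear the actigraphy devices and complete the daily sleep diary in order to monitor sleep habits during a 2-week washout period".
- **Crossover (5.4).** "Participants who were assigned to the stimulation treatment group during Visit 2 will be assigned to the sham group and vice versa". No condition on the washout data is attached. At the same visit, "Participants will take the ISI once again for a second baseline measurement".
- **Primary analysis (3.2).** Change in SOL over 14 days of treatment, in a "linear mixed effects model accounting for age, baseline SOL, ISI severity, and prior sleep medication use". The stimulation-first arm is compared with the sham-first arm, with the stated aim of keeping out lasting effects of the device.
- **Within-subject analysis (3.2).** A secondary mixed model, "which will include the order as an additional covariate". Section 5.2 defines order as sham first or stimulation first. TST, WASO, ISI and PHQ-9 are modelled similarly, and a paired t-test is one of the tests named for each measure.
- **Baselines (3.2).** "All measures will be investigated as differences from each patient’s individual baselines". It is not said whether period 2 uses weeks 1-2 or the washout.
- **Primary outcome (2.2).** The SOL reduction is measured "using FitBit actigraphy data collected during baseline, treatment, and washout periods".

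**The concern.** The washout is given a purpose, and data are collected that could serve it, but section 3.2 describes no analysis of lingering effects. The covariates of the within-subject model cannot make up for this. Age, prior medication use and order are the same in both periods for a given patient. Baseline SOL and ISI severity are most naturally read that way too. Such terms do not touch the stimulation-sham difference, and neither does subtracting one common baseline.

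At stake is the size of the within-subject effect. Section 6.1 presents the repeated-measures design, with each patient as their own control, as a notable strength. Any effect still present after two weeks would lower SOL in the sham period of the stimulation-first group and shrink that estimate. Precision available from data already planned is also left aside. Separately, sections 2.2 and 3.2 do not agree on which nights serve the primary outcome.

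**Working it through.** **Inputs.** Section 2.7 plans 60 enrolled and 48 completers at 20% attrition: 48/(1 - 0.20) = 60, which reproduces. Counterbalanced, that is 24 completers per sequence. Section 3.1 aims at a 50% reduction from an SOL above 30 min, so t = -15 min serves as illustration. The documents give no SDs. Assumed: within-patient SD 8 min per period mean, between-patient SD 10. The percentage biases do not depend on the SDs.

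**Bias without a period baseline.** Let p be the period effect and c = f·t the effect remaining in the later sham period.

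- Stimulation-first, stimulation minus sham: t - p - c
- Sham-first, stimulation minus sham: t + p
- Average: t - c/2 = t(1 - f/2)

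Order is the same on both of a patient's records, so it leaves this unchanged. A simulated mixed model with treatment, order, baseline SOL and a random patient intercept agrees:

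| f | formula | simulated | shortfall |
|---|---|---|---|
| 0 | -15.0 | -15.1 | 0 |
| 0.25 | -13.1 | -13.3 | 12.5% |
| 0.5 | -11.25 | -11.6 | 25% |
| 1 | -7.5 | -7.7 | 50% |

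The simulated first-period comparison stayed between -14.8 and -15.1 throughout.

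**Adding a period-specific baseline.** Let g be the share of the effect present in the washout baseline and b the slope on the baseline difference. The baseline differences average -g·t/2 over the two sequences, so the adjusted estimate is t(1 - f/2 + b·g/2). With equal variances b = r, the correlation of the baseline and outcome differences.

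- f = g = 0.5: -12.4 at r = 0.3 and -13.1 at r = 0.5, against -11.25 unadjusted. The bias is only partly removed, and not at all at r = 0.
- f = 0, g = 0.25 (residual gone by period 2): -15.6 at r = 0.3 and -15.9 at r = 0.5, a slight overshoot.
- Subtracting the baseline (b = 1): -15.0 if f = g, but -16.9 if the residual falls from 0.5 to 0.25.

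**Precision.** Unadjusted, a patient's difference has variance 2 × 64 = 128, and the estimate has variance (128/24 + 128/24)/4 = 2.67, SE 1.63. As a covariate the variance is multiplied by 1 - r²: SE 1.56 at r = 0.3 and 1.41 at r = 0.5. At r = 0 a simulation gave 1.67 against 1.64, so little is lost. Subtraction multiplies the variance by 2(1 - r): SE 2.31 at r = 0. This is why the baseline should be a covariate and not be subtracted.

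**Can the planned analysis reveal carryover?** The order coefficient carries c/2. For mean change from baseline its SE is √(2 × (64/2 + 64)/24) = 2.83. At f = 0.25, c/2 is 1.9 min in size, a ratio of 1.9/2.83 = 0.66. Washout minus baseline by sequence carries the whole residual, 3.75 min at g = 0.25, with SE √(2 × 128/24) = 3.27, a ratio of 1.15. That is the better signal, though its 95% half-width of 1.96 × 3.27 = 6.4 min is still wide.

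**The case against.** The strongest reply is that carryover is handled where it matters. The primary comparison is built to exclude it, the exposed comparison is labelled secondary, and the bias runs toward no effect, so it cannot manufacture a benefit. All of that stands.

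It can also be said that order in the model, the two-way ANOVA on treatment order and the primary result alongside would show any carryover. This stands only in part. The order effect is a weak between-patient signal, and at f = 0.25 the two estimates would differ by 1.9 min when the primary change-score contrast has an SE of about 3.3 under the same assumptions.

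Four stronger readings are tempting, and the documents support none of them.

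- *Residual effect is in the sham data.* Nothing shows an effect lasting beyond 14 days. It is a possibility.
- *The washout nights and Visit 4 ISI are unused.* Section 2.2 lists washout actigraphy, section 3.2 models ISI at various timepoints, and individual baselines could include a second one. Their role is unstated, which is a narrower point.
- *Washout nights are to be pooled into the primary outcome.* Pooling 14 washout with 14 treatment nights would halve the effect without carryover, (t + 0)/2. But section 2.2 lists baseline nights in the same phrase, so it reads as a list of data sources.
- *Automatic crossover is a fault.* A fixed washout with unconditional crossover is ordinary practice, and the choice of the word ensure in 5.3 is editorial.

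Finally, the form of a baseline covariate often belongs in an analysis plan, which is not at hand. That limits the weight of the point. It does not resolve the mismatch among 2.2, 3.2, 5.3 and 5.4, all of which are in the article.

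**Conclusion.** The point holds in limited form. The primary first-period comparison is not affected. The secondary within-subject comparisons, including a paired test, would be biased toward no effect by half of whatever effect remains: 12.5% of the true effect at f = 0.25 and 25% at f = 0.5. These shares are assumed, and the result rests on baseline SOL and ISI severity being single values per patient, the natural but not the stated reading.

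The period-specific covariate mainly buys precision, a variance reduction of about 9% to 25% for an assumed r of 0.3 to 0.5. It is not a cure for carryover. Sections 2.2 and 3.2 need reconciling in any case. This is a worthwhile and cheap improvement, not a threat to the main conclusion.

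**What to change.** 1. **Within-subject models (3.2).** Enter the period-specific baseline as a covariate and do not subtract it: weeks 1-2 for period 1, and the last 7 washout nights (Visit 4 ISI for the ISI) for period 2. The slope should come from within-patient differences. State that the carryover bias is only partly removed and that a slight overshoot is possible if the residual fades between washout and period 2.
2. **Residual effect (3.2).** Report washout SOL, and Visit 4 ISI, minus initial baseline, stimulation-first against sham-first, with a confidence interval beside the within-subject result. Do not use it as a gate for choosing a model: it is too imprecise. Interpret the within-subject result as conditional on negligible carryover.
3. **Primary outcome (2.2 and 3.2).** Reconcile the two so that the primary outcome uses baseline and first-period treatment nights, and assign the washout nights to the residual-effect analysis.

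The cost is wording and a small analysis of data already planned. The downsides are one more covariate, a small loss if r is near 0, and some noise if washout nights are sparse.
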